#### Pre-planned subgroup analyses

We will test for interaction between intervention and the following groups. If interaction is present, the results will presented as sub-group analyses, in particular:

• Delirium vs no delirium

• Pre-admission care home vs own home

• Acute geriatric medical ward control group vs other ward

• Died during follow up vs survived

• Index hospital length of stay >5 days vs ≤5 days.

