### Data analysis

#### Power and sample size

We used data from the prior cohort study to estimate sample size and statistical power. The Days at Home variable has a negatively skewed distribution (median 62 days at home, inter-quartile range 1 to 82 days), with 24% of participants having zero days at home. We assumed that the Mann-Whitney U test would be used to test for differences between groups. We used a bootstrapping simulation method to investigate the power of the study to detect possible effects of the MMHU, on both the probability of zero days at home and numbers of days spent there, under a range of plausible assumptions. A study with 300 participants in each group has 80% power to detect a 5 day difference in days at home, if the proportion of patients with zero days at home is reduced to 20% (a 15% reduction). This represents a reasonable minimum clinically important difference.

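### Presentation of the pre-planned subgroup results depends on an interaction being found, in a trial sized for a main effect, so the estimates that get shown will be exaggerated on average

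*Protocol article*

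**What the plan says.** Under the heading "Pre-planned subgroup analyses" the protocol article first commits to testing: "We will test for interaction between intervention and the following groups". It then makes presentation conditional: "If interaction is present, the results will presented as sub-group analyses, in particular". No threshold is given for when an interaction counts as present.

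Five factors follow:

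- whether or not the patient has delirium
- whether the patient lived in a care home before admission
- the type of ward in the control arm, worded as "Acute geriatric medical ward control group vs other ward"
- vital status, worded as "Died during follow up vs survived"
- length of the index stay, split at five days

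The sample size rests on the overall comparison alone. In Power and sample size: "A study with 300 participants in each group has 80% power to detect a 5 day difference in days at home", on the condition that the proportion with zero days falls to 20%. No power is stated for any interaction.

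**The concern.** If the rule is followed as written, readers see subgroup estimates for pre-planned factors after a positive interaction test and have no assurance of seeing them otherwise. That is selection on the result. When the test has low power, the estimates that pass are too large on average, and real differences of moderate size usually fail to pass.

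The rule also differs from the article's own practice elsewhere. The analysis sections promise differences and the intervention effect with 95% confidence intervals, without any condition on significance.

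At stake are statements about which patients benefit from the specialist unit. The problem applies even to the two sound factors, delirium and prior care home residence, so removing unsuitable factors from the list would not cure it.

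**Working it through.** **Inputs from the article.** 300 per group; 1:1 allocation; 80% power for 5 days; cohort median 62 days, quartiles 1 and 82, 24% zeros; Mann-Whitney test, with power found by bootstrap.

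**Assumptions.** Two-sided 5% level (not stated; inferred from the 95% intervals). Normal approximation. Subgroup fractions f from 0.5 to 0.2, because the article gives none.

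**The plan's own figure.** The cohort data are not shown, so I rebuilt the distribution from the stated zeros and quartiles with three assumed shapes and simulated the Mann-Whitney test.

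- A 5-day shift in the non-zero values, with zeros at 20 to 20.4%, gives 84 to 90% power.
- A smaller shift, giving an overall mean difference of about 4.7 to 4.8 days, gives 64 to 65%.

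The stated 80% lies between these readings. It is neither confirmed nor shown to be wrong, so I use two scales below.

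**Scale A: the stated 80% at face value.** Main-effect SE = 5 / (1.96 + 0.84) = 1.79 days. For a subgroup of fraction f, interaction SE = main-effect SE / sqrt(f(1 − f)). The true interaction is set at 5 days, the size of the main effect.

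| f | Interaction SE (days) | Significant beyond (days) | Power | Mean size if significant, relative to truth |
|---|---|---|---|---|
| 0.5 | 3.57 | 7.0 | 29% | 1.8 |
| 0.3 | 3.9 | 7.6 | 25% | 2.0 |
| 0.25 | 4.1 | 8.1 | 23% | 2.1 |
| 0.2 | 4.5 | 8.7 | 20% | 2.3 |

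At f = 0.5, 80% power for such an interaction would need 1/(0.5 × 0.5) = 4 times the sample. At f = 0.2 it would need 1/(0.2 × 0.8) = 6.25 times.

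**Scale B: assumed SD of 35 days.** The three reconstructions give SDs of 34.6 to 36.5.

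- Even split: SE = 35 × sqrt(4/150) = 5.72; threshold 1.96 × 5.72 = 11.2 days; power for 5 days 14%; mean absolute estimate when significant 14.1 days, or 14.1/5 = 2.8 times the truth.
- 25/75 split: SE = 35 × sqrt(2/75 + 2/225) = 6.60; threshold 12.9 days; power 12%; mean 16.1 days, or 3.2 times.

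Scale B conflicts with the stated power if the comparison is one of means. The main-effect SE would be 35 × sqrt(2/300) = 2.86, and 5/2.86 = 1.75 standard errors gives about 42% power. Scale B is therefore the pessimistic end of the range.

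**False interactions.** Two valid factors, one outcome, no true interaction: 1 − 0.95² = 9.75% if the tests are independent, and 9.1% at a correlation of 0.5.

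**The case against.** The rule has real merits. The factors are listed in advance, and an interaction test is required before subgroups are interpreted, which is better than separate within-subgroup p-values. Both points stand. They support using the test to guide interpretation; they do not justify letting it decide what is shown.

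Several stronger readings are tempting, and the document does not support them:

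- **That negative results will be hidden.** The article promises every interaction test and makes only the subgroup presentation conditional. It does not say that non-significant interaction estimates will be withheld; it simply does not commit to showing them.
- **That outcome restriction, multiplicity control and an exploratory label are missing.** An article commonly leaves these to the analysis plan or full protocol, neither of which is shown.
- **That five tests give about a 23% chance of a false interaction.** The control-ward factor exists in one arm only, so no interaction with treatment can be formed. Death and index length of stay arise after randomisation and are components of days at home, so they are not valid treatment-effect subgroups. The figure that matters here is for two factors.
- **That an interaction must exceed twice 5 days to count as present.** This holds at SD 35. At the stated power the multiple is 1.4 for an even split (7.0/5) and 1.6 for 25/75 (8.1/5).
- **That any subgroup shown must be false or grossly inflated.** On scale A, a true 10-day interaction has 61 to 80% power across the fractions considered and is inflated by only about 13 to 28%.

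**Conclusion.** The point holds in limited form. The article fixes a results-dependent presentation rule for pre-planned subgroups, and its sample size gives interaction tests little power: 20 to 29% for an interaction the size of the main effect at the stated power, and 12 to 14% for 5 days at SD 35. Estimates passing the filter would be inflated on average about 1.8 to 2.3 times on the first scale and about threefold on the second. The chance of at least one false interaction among the two valid factors is 9 to 10% per outcome.

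These sizes depend on the assumed 5% level, the subgroup fractions and the normal approximation. The direction is the same in every scenario tried. The primary analysis is not affected. The change is worth making because it costs almost nothing.

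**What to change.** Replace the conditional sentence. For each valid baseline-defined factor (delirium and pre-admission care home residence), report on days at home the interaction estimate with its 95% CI, and the within-subgroup estimates, whatever the test result. State that the test only guides interpretation and that a non-significant interaction is not evidence of no interaction. Because delirium is recorded after allocation, by staff who know it, say so beside that result.

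This does not lower the 9 to 10% chance of a false interaction. It lets readers see every estimate with its uncertainty rather than a selected few. The cost is a sentence of plan wording, a few more table rows and more cautious subgroup statements.

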### Secondary hypotheses

Compared with standard care, management on the MMHU will be associated with:

1. lower mortality

2. better quality of life, less behavioural disturbance, and less disability after 90 days

3. fewer readmissions, reduced total hospital stay over 90 days, and fewer new care home placements

4. greater satisfaction with hospital care amongst family carers

5. less carer strain and psychological dysfunction.

Management on the MMHU is cost-effective compared with standard care.

Management on the MMHU is associated with better quality of care and patient experience in a concurrent observational study.

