### Overview of study design

Potentially suitable patients are referred to MMHU by clinical staff on the Acute Medical Admissions Units, within 24 hours of admission. MMHU staff record details on a computerised screening log. An algorithm allocates patients either to MMHU or a standard care ward, some at random, others not (Figure 1). If allocated to MMHU the patient is transferred immediately. If allocated standard care, an alternative bed is found by Admissions Unit staff.

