### Outcome measurements

#### Definition of primary and secondary outcomes

The primary outcome is number of days spent at home (or in the same care home) in the 90 days following randomisation [10]. This is calculated as 90 days minus days spent dead, in hospital, intermediate care, or a new care home.

It is assumed that discharge home and successfully maintaining it is the goal of health care in this context, taking account of mortality, and readmission, and is a suitable high level summary of the success or failure of hospital acute care.

Secondary outcomes are:

• Mortality

• Quality of life, measured using the dementia-specific Demqol patient and proxy scales [23]; Euroqol EQ5D [16]; and short London Handicap Scale [24]

• Behavioural and psychological symptoms (Neuropsychiatric Inventory [18])

• Carer satisfaction with hospital care (from [2])

• Physical disability (Barthel index [17])

• Cognitive impairment (Mini-Mental State Examination [14])

• Readmission, and total hospital length of stay

• Place of residence

• New care home placement

• Carer strain index [20]

• Carer psychological distress (GHQ-12 [21])

• Health and social care resource use, using the Client Service Receipt Inventory [25] and from routine health and social care records.

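### Three of the five pre-planned interaction tests (death, index length of stay, control-ward type) cannot give a valid effect-modification result

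*Protocol article*

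**What the plan says.** Under Pre-planned subgroup analyses the article states: "We will test for interaction between intervention and the following groups". If an interaction is found, subgroup results are to be presented. Five groupings follow under this one rule. Three matter here: "Acute geriatric medical ward control group vs other ward", "Died during follow up vs survived" and "Index hospital length of stay >5 days vs ≤5 days". The other two are delirium and pre-admission care home residence.

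The primary outcome is days at home, or in the same care home, over 90 days from randomisation. Under Definition of primary and secondary outcomes: "This is calculated as 90 days minus days spent dead, in hospital, intermediate care, or a new care home".

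Secondary hypotheses expects the MMHU to bring "lower mortality" and "fewer readmissions, reduced total hospital stay over 90 days, and fewer new care home placements".

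Under Overview of study design, referral happens "within 24 hours of admission" and allocation follows. For a patient allocated to standard care, staff of the Admissions Unit then look for a bed elsewhere. Standard care lists four acute geriatric and six general medical wards.

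**The concern.** An interaction test asks whether the treatment effect differs between kinds of patient. It needs a factor that exists in both arms and that treatment cannot have altered. Care home residence before admission, the stratification factor, meets both conditions.

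Death and index stay fail the second condition if the unit works through them. Suppose a patient would stay 6 days on a standard ward and 4 days on the MMHU. That patient falls in the longer-stay stratum under one allocation and the shorter-stay stratum under the other. Likewise, a patient whose life the unit saves joins the survivors only in the MMHU arm. The arms within a stratum then differ in case mix, and randomisation no longer protects the comparison. The outcome also subtracts days dead and days in hospital, so patients are being grouped on parts of their own outcome.

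Control-ward type fails the first condition, because no MMHU patient has a value for it.

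At stake are three of five pre-specified tests. A reader would take their results as planned evidence on who benefits from the unit, which they cannot supply.

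**Working it through.** The article gives no figure for these subgroups, so there is none to reproduce. All inputs on mortality, stay and frailty below are assumptions.

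**1. Ward type.** The interaction model has four columns: intercept, T (1 = MMHU), W (ward type) and T×W. MMHU patients have no W, so some code must be imposed.
- Coded 0: T×W is zero for everyone.
- Coded 1: T×W equals T.

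Either way the matrix has rank 3 of 4 (confirmed numerically with 300 per arm), so the interaction coefficient does not exist. For a factor present in both arms, such as care home residence, the rank is 4 of 4.

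**2. Death, by arithmetic.** Assume mortality of 25% under standard care and 20% on the MMHU. Those who would survive in either arm average 60 home days, those saved average s, and those who die have none.
- Apparent effect in survivors = (0.75×60 + 0.05×s)/0.80 − 60
- True overall effect = 0.05×s

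| s | Survivors | Overall |
|---|---|---|
| 10 | −3.1 | +0.5 |
| 20 | −2.5 | +1.0 |
| 30 | −1.9 | +1.5 |

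**3. Death and index stay, by simulation** (2,000,000 patients). Z and each e are independent standard normals, with Z for frailty.
- Control death probability is the inverse logit of −1.35 + 1.2Z (about 26% die). Time of death is uniform over days 1 to 90.
- Index stay is 8×exp(0.4Z + 0.8e) days.
- Later loss of home days is 10 + 12Z + 10e, bounded at 0 and 90 and scaled by time alive/90.
- Days at home are time alive minus stay minus later loss, bounded at 0 and 90.
- Treatment acts only by multiplying death risk or stay.

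| Treatment effect | Overall | Died | Survived | Stay ≤5 | Stay >5 |
|---|---|---|---|---|---|
| None | 0.0 | 0.0 | 0.0 | +0.1 | 0.0 |
| Death risk −25% | +2.0 | 0.0 | −1.1 | – | – |
| Death risk −50% | +4.1 | −0.1 | −2.0 | – | – |
| Stay −20% | +2.0 | – | – | −0.8 | +0.6 |
| Stay −40% | +4.1 | – | – | −1.8 | +0.8 |

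Treated survivors are frailer than control survivors by 0.08 SD (25% cut) and 0.14 SD (50% cut). That gap in case mix is the source of the bias.

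**4. Index stay under other assumptions** (lognormal stay, median 11 days). These parameter settings are not listed here, so they show a range only.
- Every stay shortened by 2 days, six settings: overall about +1.5 to +1.9. In five settings both strata were negative (≤5 days −0.06 to −0.63; >5 days −0.84 to −1.90). In the sixth they were +0.2 and −0.5.
- Every stay shortened by 20%: ≤5 days −0.3 to −0.8; >5 days +1.0 to +2.1.

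**5. How often would the bias produce a significant interaction?** Power and sample size reports 24% zeros and quartiles of 1, 62 and 82. A piecewise-linear distribution fitted to these has an SD of about 35 days. With 300 per arm and a fraction p in the short-stay stratum, SE = 35×√[(2/300)/(p(1−p))]. This is 5.7 at p = 0.5 and 6.6 at p = 0.25.
- Stay, uniform shortening, a setting with strata at −0.49 and −1.12: gap 0.63, z about 0.1, rejection close to the nominal 5%.
- Stay −40%: gap 0.75 + 1.75 = 2.5, z about 0.4, rejection about 7%.
- Death, spurious gap of 1.9 to 3.1 days, 225 and 240 survivors, 75 and 60 deaths. With SDs of 25 (survivors) and 15 (dead), SE = √[25²(1/225 + 1/240) + 15²(1/75 + 1/60)] = 3.5. With both SDs at 36, SE is 7.1. Rejection is 6% to 14%.

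**The case against.** The best defence is that these tests are secondary and conditional. Subgroups are shown only if an interaction is present, and step 5 shows that the bias alone would trigger that rule only a little more often than chance. A reader might infer that the plan will publish an artefact. The documents support only that it could. All the distortions shown are also below the 5-day difference used for the sample size.

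A reader might also infer that an effective unit would look harmful in every stratum. That is not a general result. It appears under most settings of a uniform 2-day shortening, but under proportional shortening the longer-stay stratum keeps the right sign. For death, the difference among those who died is about zero.

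Nor does the protocol hypothesise a shorter index stay. Its hypothesis concerns total hospital stay over 90 days, which includes readmissions. An effect on index stay is a plausible inference, but not a stated aim.

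Finally, ward type may have been meant as MMHU against each kind of control ward. That can be computed and is of interest. It is a three-group contrast, however, and the control ward is not chosen at random.

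These points limit the size and likelihood of harm. They do not make the three tests valid, and the article states no descriptive or mechanistic purpose that would excuse them.

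**Conclusion.** The point holds, as something that should be fixed rather than a fault in the trial's main result. The ward-type interaction cannot be fitted, and this needs no assumption. The death and stay tests are biased if the MMHU changes death or index stay. The protocol hypothesises the former, and the latter is a fair inference.

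Under the assumed inputs, survivors show about −1 to −3 days against a true overall effect of +0.5 to +4 days. The stay strata range from about +0.2 to −1.8 (≤5 days) and −1.9 to +2.1 (>5 days). Only the presence of distortion is secure, since its size and sign rest on the model. With no effect on death or stay, the differences stay within 0.1 day of zero.

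It would be wrong to conclude that the trial's primary answer is compromised. The comparison of days at home between all recruited patients does not use these strata, and mortality and hospital stay are separately listed as outcomes.

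**What to change.** - Delete death during follow-up and index length of stay as interaction or subgroup factors. Little is lost, because both mortality and total hospital stay are already compared between the arms as secondary outcomes.
- Replace the ward-type interaction with a comparison of the MMHU with each control-ward type. Label it exploratory and non-randomised, and adjust it for baseline characteristics.
- Keep interaction tests for characteristics that pre-date allocation, such as care home residence.
- Add a caveat on delirium. Baseline data are collected after ward allocation, and Allocation concealment says the staff collecting them know the allocation, so this factor is not fully protected either.

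The cost is a change of wording in the analysis section, with no new data and no effect on sample size.

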#### Economic analyses

Costs will be constructed from the perspective of the NHS and personal social services. Ninety days of resource data will be collected for each patient participant. Costs for each participant will be calculated as resource use multiplied by the unit cost of the specific resource, valued using published unit cost data.

A cost-effectiveness analysis comparing the MMHU to standard care will be carried out using standard methods. Incremental cost-effectiveness analysis will be undertaken in the absence of convincing dominance by any treatment alternative. Benefits to the patient participant will be measured with Quality-Adjusted Life Years (QALYs), which will be generated using EQ5D data, assuming homogeneity across treatment groups in any insensitivity of the EQ5D to our patient participants. These will be combined with cost data to generate Incremental Cost-Effectiveness Ratios and Incremental Net Benefit statistics. No discounting will be necessary given the short follow-up time.

Sensitivity analyses and cost-effectiveness acceptability curves will be used to assess uncertainty in the estimated incremental net benefit statistics.

### Project management and administration

#### Project management

Overall supervision of the trial is by the Medical Crises in Older People Programme Management Board, which meets monthly, chaired by the programme Principal Investigator (JG).

In addition, a Trial Steering Committee has been constituted, with an independent chair, three independent professional members (one psychiatrist, one physician, one social scientist), two independent lay members, and three trial investigators, including the statistician.

Day to day management of the project is by a trial manager (SG), supervised by the chief investigator (RH), and assisted by research assistants (KW and CR). The trial is also supported by research assistants employed by the National Institute for Health Research Comprehensive Local Research Network, Mental Health Research Network, and the Trent Dementia Research Network.

The trial sponsor is the University of Nottingham.

#### Trial documents

The documents to be completed, and by whom, are recorded in table 1.

**Table 1 T1:** Trial documentation

Form title	Completed by
Screening log (computerised)	MMHU ward nurses

Capacity assessment form	Researcher

Patient participant information and consent forms	Patient with capacity to consent

Consultee information and agreement forms	Family member of carer (on behalf of patient without capacity to consent)

Carer participant information and consent forms	Family member or carer

Professional information and agreement forms	Nurse in charge of ward (on behalf of patient without capacity to consent and with no contactable carer)

Identifiable data form	Researcher

Patient participant initial data form	Researcher

Carer initial data form	Family member or carer/researcher

Medical data form (from casenotes)	Researcher

Dementia care mapping raw data sheets	Researcher

Patient participant follow-up data form	Researcher

Carer follow-up data form	Family member or carer/researcher

Resource use from computerised records	Health economist

Health care intervention form	Medically qualified researcher

#### Ethical approval

The protocol was given a favourable opinion by the Nottingham 1 Research Ethics Committee (reference 10/H0403/16).

#### Project milestones

Project milestones are described in table 2.

**Table 2 T2:** Project milestones

From	To	Activity
2006	2008	Programme planning and funding application

Feb 2009	July 2010	Planning, development and maturation of MMHU intervention

May 2009	June 2010	Recruitment and follow up of cohort (case series), pilot study for the trial

February 2010		Submission to Research Ethics Committee and Hospital Research governance

May 2010	July 2010	Pilot random allocation to MMHU or standard care

July 2010	December 2011	Trial recruitment (possible extension to July 2012)

October 2010	March 2012	Follow up

January 2011	December 2011	Non participant observer study

March 2012	October 2012	Final data cleaning, analysis, write up

April 2013		Service support funding ceases

July 2013		Research funding ceases

